## Methods

### Study Population

East Sumba District was selected as the study area because it is classified as a high malaria-endemic region [64]. The district consists of 22 subdistricts and 156 villages [65]. The total population in the district is 248,776, with an almost equal distribution of male (51.4%) and female (48.6%) residents. Approximately one-half of the population is engaged in the agricultural sector. The district has 4 hospitals, 22 public health centers, and 78 subsidiary public health centers across the region [65]. This study was conducted in 4 selected subdistricts where there is 1 public health center in each subdistrict, as indicated in Figure 1.

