### Study Design and Sampling Technique

This study used a cluster-assigned quasi-experimental design with pretest and posttest assessments in both control and intervention groups. The cluster unit for this study was the village, which was not randomized because the research team aimed to implement the intervention across all villages within a selected subdistrict, where the subdistrict leader would serve as a role model to encourage the community to improve malaria awareness. To obtain a representative sample, the research team randomly selected 4 of the 22 subdistricts, of which 2 were assigned as the intervention groups and 2 served as the control groups. The first 3 subdistricts each had 6 villages, and the fourth subdistrict had 7 villages; therefore, a total of 25 villages participated in the study, representing about 16% of all the villages in the district. Of these, 13 villages were assigned to the intervention group, while 12 villages formed the control group. The number of sampled households selected from each village was proportional to the number of households in that village. Within each selected village, households were randomly sampled to serve as an experimental unit as indicated in Figure 2.

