First, the research team met with the subdistrict head and village leaders in the 2 selected subdistricts designated as the experimental areas. After obtaining their approval, the research team recorded a campaign message delivered by each subdistrict leader. The campaign content, developed by experts in malaria-related behavior, mathematical modeling, and rural development, included the main symptoms of malaria, prevention strategies, and the appropriate treatment-seeking behavior for suspected malaria cases. During the campaign, the subdistrict head occasionally emphasized key points in the local language to improve comprehension. The recorded message was then combined with a locally popular song to enhance engagement. The final recording was 15 minutes long. Second, 6 health promotion staff members from Baing and Mahu Public Health Centers were selected as RAs to play the recording. The recording was broadcast using loudspeakers to ensure wide community outreach. Third, the RAs played the recorded message once per week for 20 weeks in the 13 intervention villages. The intervention started in the fourth week of August 2024 and concluded in the second week of January 2025. In each selected village, the intervention was conducted in 4 different locations per week to ensure that all community members were reached. The principal investigator maintained weekly communication with the RAs to ensure that the intervention was being conducted properly. Over the 20-week intervention period, the research team monitored implementation by visiting the experimental villages once a month for 5 months.

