### Independent Variables of the Study

This study considers demographic and environmental factors as independent variables. Demographic variables include gender, age, education level, occupation, and socioeconomic status (SES). Respondents’ SES will be measured based on ownership of durable assets such as a television, refrigerator, car, electricity, telephone, and radio; the number of bedrooms; and home infrastructure conditions such as access to drinking water sources and the presence of water channels around the house [68]. Using principal component analysis, respondents’ SES will be categorized into 5 quantiles ranging from the lowest (quantile 1) to the highest (quantile 5) [69]. Environmental variables in the study include the location of the residence, categorized as rice fields, coastal areas, or hilly areas, and accessibility to villages, classified as easy, moderate, or difficult to access. Additionally, the study considered proximity to health facilities, including the type and distance of the nearest health facilities. For secondary data from the health center, patient records from 2013 to 2023 were reviewed for all patients with suspected malaria, and positive or negative cases were confirmed based on laboratory examination results. The number of malaria cases based on gender, age group, type of *Plasmodium*, time (year and month), location of residence, and type of treatment and the number of deaths since the period under review were collected from the 4 selected health centers.

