The seventh outcome variable in this study is variation in access to basic drinking water and its associated factors among rural communities in ENT Province, Indonesia. Household access to basic drinking water is defined based on the WHO Joint Monitoring Program guidelines, which classify water sources into 4 categories: no service, unimproved, limited, and basic [75]. To analyze this variable, a dichotomous classification will be used, where households will be categorized as either having access to an improved drinking water source (Yes=1) or lacking access to an improved drinking water source (No=0). This classification will help determine disparities in access to safe drinking water and identify key factors influencing these differences.

The secondary outcomes of this study are derived from the analysis of patient medical records from 4 selected health centers, along with additional data from the Department of Health, East Sumba District. The eighth outcome variable focuses on the monthly number of malaria cases recorded over the past 10 years, from 2013 to 2023. By integrating data from both health centers and the Meteorological Agency of East Sumba, this study aims to explore the impact of climatic variables on malaria case fluctuations in this region, following the methodology of a previous study [76]. This analysis will provide valuable insights into seasonal and long-term trends in malaria transmission, which could help inform future malaria prevention and control strategies.

The ninth outcome variable in this study examines the demographic variations in malaria prevalence among communities residing in hilly and coastal areas over the past 10 years (2013-2023). Among the 4 selected health centers, Baing and Nggongi Public Health centers are located in coastal areas, whereas Mahu and Kananggar Public Health Centers are situated in hilly regions. Given that vector distribution and species composition may vary between different geographic settings [77], previous studies in Indonesia have reported significant differences in malaria prevalence between coastal and hilly areas [78]. By analyzing malaria case records from these health centers, this study aims to assess regional disparities in malaria burden and determine how demographic and environmental factors contribute to these differences. This information may help tailor malaria prevention and control efforts to the specific needs of different geographic regions.

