For the ninth outcome variable, malaria cases records from 2013 to 2023 will be analyzed across different geographic areas. Data from Baing and Nggongi Public Health Centers, representing coastal regions, will be combined, while records from Mahu and Kananggar Public Health Centers, representing hilly areas, will be aggregated separately. Malaria prevalence will be calculated on a monthly, yearly, and cumulative basis over the study period. To visualize the demographic trends, malaria prevalence will be plotted against key demographic variables. The disparity of malaria prevalence in demographic variables will be investigated using a chi-square test [10,82].

For the tenth outcome variable, descriptive statistics will be used to calculate frequencies and percentages of overall malaria prevalence and trends in malaria transmission considering variations by season, month, year, sex, age, and species of malaria parasite. Epidemiological characteristics, including age group, sex, and *Plasmodium* species–adjusted malaria-related mortality rates in East Sumba District will be presented as percentages followed by their 95% confidence intervals. Chi-square tests will be used to compare the associations of malaria burden by age groups and sex. The malaria prevalence and mortality rate will be illustrated in a map to assess the distributions of the cases geographically [79,80].

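### Coastal versus hilly rests on two health centers against two in outcome 9, and may be one subdistrict against one within each arm's survey models, so terrain cannot be separated from site

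*Protocol article*

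**What the plan says.** Study Population and Study Design and Sampling Technique fix the structure: "This study was conducted in 4 selected subdistricts where there is 1 public health center in each subdistrict", and the team "randomly selected 4 of the 22 subdistricts, of which 2 were assigned as the intervention groups and 2 served as the control groups".

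Phase III (Intervention Stage) shows which centers serve the campaign area: "6 health promotion staff members from Baing and Mahu Public Health Centers were selected as RAs to play the recording". Outcome Variables gives the terrain: "Baing and Nggongi Public Health centers are located in coastal areas, whereas Mahu and Kananggar Public Health Centers are situated in hilly regions".

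For the ninth outcome, Statistical Analysis gives the handling of the coastal side first: "Data from Baing and Nggongi Public Health Centers, representing coastal regions, will be combined". The hilly side is treated in the same way: "records from Mahu and Kananggar Public Health Centers, representing hilly areas, will be aggregated separately". Outcome Variables gives the purpose as to "assess regional disparities in malaria burden and determine how demographic and environmental factors contribute to these differences", and says the result may help fit malaria control to geographic areas.

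For the survey, Independent Variables of the Study lists the covariate: "Environmental variables in the study include the location of the residence, categorized as rice fields, coastal areas, or hilly areas, and accessibility to villages". Statistical Analysis calls it household location and plans ordinary binary logistic regression in both study groups to find associated factors. No subdistrict term is mentioned.

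**The concern.** A subdistrict differs from its neighbour in more than terrain. By the plan's own account, each has its own health center giving the routine malaria education. Each campaign subdistrict also has its own leader, who recorded a separate message and is meant to act as a role model. Enumerators were drawn from the selected health centers, so interviewer habits may follow subdistrict too.

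When only one or two sites stand for each terrain, a coastal-hilly difference carries all of this with it. More respondents or more register entries per site do not help, because the number of sites is what limits the inference. The risk is that a difference between particular places is published as an effect of coastal or hilly living and then used to direct control efforts by terrain. The limitations in the Discussion do not mention this.

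**Working it through.** **The plan's own figure.** 1.96² × 0.488 × 0.512 / 0.05² = 383.94, rounded up to 384; × 2 = 768; × 1.15 = 883.2, rounded up to 884. The stated sample size reproduces and is not at issue here.

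**Layout of sites.** There is one center per subdistrict and two subdistricts per arm. Staff from Baing and Mahu play the recording, so by inference these are the campaign subdistricts and the other two are controls.

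| Arm (inferred) | Coastal center | Hilly center |
|---|---|---|
| Intervention | Baing | Mahu |
| Control | Nggongi | Kananggar |

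**Outcome 9, two centers against two.** With the center as the unit:
- The four centers can be split into two pairs in C(4,2) = 6 ways, so the smallest two-sided exact permutation P is 2/6 = 0.33.
- A t comparison of center values has 4 − 2 = 2 degrees of freedom, with a critical value of 4.30 in place of 1.96.

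The pooled figures also hide how far apart the two centers of the same terrain are, which is the only information on between-center spread.

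**Survey, within one arm.** If every household had its center's terrain, the contrast would be one subdistrict against one, with 0 degrees of freedom for between-subdistrict error. The error rate of a naive test can then be computed.
- Inputs: 894 respondents in a survey (Results), split evenly by assumption, so m = 894/4 = 223.5 per subdistrict; two-sided 5% level; between-subdistrict intracluster correlation (ICC) assumed, because the plan gives none.
- Design effect: DEFF = 1 + (m − 1) × ICC.
- False-positive rate: 2 × [1 − Φ(1.96/√DEFF)].

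| Assumed ICC | DEFF | False-positive rate (formula) | Simulation |
|---|---|---|---|
| 0.001 | 1.22 | 7.6% | not run |
| 0.005 | 2.11 | 17.7% | 17.3% |
| 0.01 | 3.23 | 27.5% | 26.9% |
| 0.02 | 5.45 | 40.1% | 40.4% |

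The simulation used 100,000 runs, beta-binomial with mean 48.8%, 223 against 224 respondents.

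**Incomplete overlap.** Let a be the share of coastal respondents, and b the share of hilly respondents, who live in the coastal subdistrict. The crude coastal-hilly difference then carries (a − b) times the subdistrict difference. It carries all of it when a = 1 and b = 0, and none when a = b. The table is therefore an upper case for each ICC, and mixing within subdistricts lowers the rates.

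**The case against.** The strongest reply is that the survey variable describes where the household is, not where the health center stands. It has three levels, including rice fields, and nothing says it is assigned from the subdistrict or constant within one. That stands. A reader might infer that the coastal-hilly term simply is one subdistrict against another; the documents support only a possible, perhaps strong, overlap.

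Second, the ICCs are assumptions, and the plan's correction factor of 2 does not supply one. It is not tied to a cluster level, and the sampling section names the village as the cluster unit. At 894/25 = 35.8 respondents per village, a factor of 2 implies an ICC of 1/34.8 = 0.029 between villages, which says nothing direct about subdistricts. This also stands, so a range is shown.

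Third, the chi-square test for outcome 9 is stated for demographic variables, not for coastal against hilly. A reader might infer that a terrain test is planned and attach a false-positive rate to it. The plan states no such test, and gives neither case counts nor between-center spread from which a rate could be derived. What survives is the pooling and the stated intention to explain regional differences by environmental factors, which needs no test to mislead.

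Fourth, it would go too far to say that any subdistrict difference will be reported as a risk factor. That depends on the test result and on other covariates, such as accessibility and distance to facilities.

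**Conclusion.** The point holds in limited form. For outcome 9 it follows directly from the text: two centers against two cannot separate terrain from other differences between centers, and no exact test at that level can go below P = 0.33.

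For the survey it is conditional. If household location follows subdistrict completely, the naive false-positive rate is about 8% to 40% for ICCs of 0.001 to 0.02 with about 223 respondents per subdistrict; it is lower if residence varies within subdistricts. This rests on the assumed ICCs, an even split of 894, and the inference about which centers serve which arm.

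A reader might also infer that the campaign effect is biased. The documents do not support that: on the inferred layout each arm has one coastal and one hilly subdistrict, so terrain by center site is balanced. The damage is confined to the associated-factor models and a secondary outcome.

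**What to change.** For outcome 9:
- Report all four centers separately beside the pooled figures. Registers were reviewed center by center, so no new data are needed.
- Give no P value for coastal against hilly, and label any terrain statement descriptive and hypothesis-generating.
- Do not let agreement in direction license a stronger claim. Both coastal centers fall on the same side of both hilly ones by chance in 2/6 = 33% of orderings if the centers are exchangeable.

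For the survey:
- Cross-tabulate household location by subdistrict before modelling.
- Add one subdistrict indicator to each arm's associated-factor model, so that only residence contrasts within a subdistrict are tested.
- Where location does not vary within a subdistrict, report it descriptively and do not name it a risk factor.
- Do not put the subdistrict indicators into a pooled model that estimates a post-intervention between-arm term. Subdistricts are nested in arms, so the indicators are collinear with arm and that term would be lost.

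The cost is one cross-tabulation, one extra term per arm model and four columns in the outcome 9 table. The coastal-hilly factor may lose precision, or its P value altogether.

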### Outcome Variables

The study considers 10 potential outcomes variables, with the first 7 serving as the primary outcomes of the intervention, while the remaining 3 represent secondary findings. The first primary outcome of the study is improvement in the malaria awareness index among rural communities. If the malaria awareness index after the intervention is higher than that before the intervention, it indicates that the health education campaign effectively enhanced malaria awareness. This index will be assessed based on 12 questions covering general knowledge of malaria, treatment-seeking behavior, and knowledge of malaria prevention measures, following the methodology of a previous study [39]. Each correct response will be assigned a score of 1, while incorrect answers will receive a score of 0, with a total possible score of 12. Participants’ knowledge level will be categorized based on their accuracy rate: 0% (zero awareness), 1% to 59% (poor awareness), 60% to 79% (good awareness), and at least 80% (excellent awareness). Those classified as having excellent or good awareness will be considered aware of malaria, while participants in the other categories will be classified as unaware of malaria [39,70]. The malaria awareness index will be calculated before and after the intervention in both the intervention and control groups to evaluate the effectiveness of the health education campaign.

The second outcome variable in this study is improvement in AMTSB. This improvement will be demonstrated if the proportion of rural adults exhibiting AMTSB after the intervention is higher than before the intervention. AMTSB is defined as seeking malaria treatment at professional health facilities within 24 hours of experiencing malaria symptoms [41]. The proportion of rural adults engaging in AMTSB will be calculated both before and after the intervention in both the intervention and control groups. This assessment will be based on the 3 key questions from the malaria treatment-seeking behavior section of the questionnaire.

The third outcome variable in this study is improvement in good MPMK. This improvement will be demonstrated if the percentage of the rural population with good MPMK after the intervention is higher than before the intervention. A good level of MPMK is defined as the ability to correctly answer at least one-half of the total questions in the MPMK section, as indicated in previous studies [41,59]. The level of MPMK will be assessed before and after the intervention in both the intervention and control groups.

The fourth outcome variable is the use of bed nets during the dry season in high malaria-endemic settings. Community behaviors regarding bed net use may exhibit seasonal variations, as individuals may adjust their practices depending on weather conditions [71]. This outcome will be assessed based on the participants’ self-reported responses to a survey question asking whether they slept under a bed net the night before the survey.

The fifth outcome variable in this study is the variation in the use of a bed net in the dry and wet seasons. The literature indicates that bed net use might fluctuate based on seasonal weather conditions, as individuals adapt their malaria prevention behaviors accordingly [71,72]. This malaria awareness campaign began at the end of August 2024, during the dry season, and concluded in the second week of January 2025, which corresponds to the wet season in the study area. The study will examine seasonal differences in bed net use by analyzing responses to 4 key questions from the malaria prevention practice section of the questionnaire. The disparity in bed net use between dry and wet seasons will be assessed for both the intervention and control groups.

The sixth outcome variable in this study is improvement in good MPMP. Improvement will be demonstrated if the percentage of the rural population practicing good MPMP after the intervention is higher than before the intervention. A good level of MPMP is defined as the ability to correctly answer at least one-half of the total questions in the MPMP section, as indicated in a previous study [73,74].

The seventh outcome variable in this study is variation in access to basic drinking water and its associated factors among rural communities in ENT Province, Indonesia. Household access to basic drinking water is defined based on the WHO Joint Monitoring Program guidelines, which classify water sources into 4 categories: no service, unimproved, limited, and basic [75]. To analyze this variable, a dichotomous classification will be used, where households will be categorized as either having access to an improved drinking water source (Yes=1) or lacking access to an improved drinking water source (No=0). This classification will help determine disparities in access to safe drinking water and identify key factors influencing these differences.

The secondary outcomes of this study are derived from the analysis of patient medical records from 4 selected health centers, along with additional data from the Department of Health, East Sumba District. The eighth outcome variable focuses on the monthly number of malaria cases recorded over the past 10 years, from 2013 to 2023. By integrating data from both health centers and the Meteorological Agency of East Sumba, this study aims to explore the impact of climatic variables on malaria case fluctuations in this region, following the methodology of a previous study [76]. This analysis will provide valuable insights into seasonal and long-term trends in malaria transmission, which could help inform future malaria prevention and control strategies.

The ninth outcome variable in this study examines the demographic variations in malaria prevalence among communities residing in hilly and coastal areas over the past 10 years (2013-2023). Among the 4 selected health centers, Baing and Nggongi Public Health centers are located in coastal areas, whereas Mahu and Kananggar Public Health Centers are situated in hilly regions. Given that vector distribution and species composition may vary between different geographic settings [77], previous studies in Indonesia have reported significant differences in malaria prevalence between coastal and hilly areas [78]. By analyzing malaria case records from these health centers, this study aims to assess regional disparities in malaria burden and determine how demographic and environmental factors contribute to these differences. This information may help tailor malaria prevention and control efforts to the specific needs of different geographic regions.

The tenth outcome variable in this study investigates malaria prevalence and malaria-related mortality rates in East Sumba district over the past 10 years (2013-2023). Data on the number of malaria cases and malaria-related deaths were obtained from malaria register books at the health centers and malaria reports from the Health Department of East Sumba District. Therefore, the trends in malaria prevalence and mortality rates over the 10-year period in the study area will be revealed, following the methods of previous studies [79,80].

